### Primary Outcome

#### Open-Road Course Driving Performance Test

Our standardized road course is a fixed route in Gainesville, Florida, with a gradual progression of driving difficulty. The scoring mechanism is based on errors, which are used to evaluate driving maneuvers. A standardized scoring sheet with a total of 49 driving maneuvers and 8 types of possible driving errors is used by the certified driver rehabilitation specialist (CDRS) or driver rehabilitation therapist (DRT) while the participant is driving. The driving errors are defined in the subsequent subsections.

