### Study Setting and Recruitment

Participants will be recruited from Medical Marijuana Treatment Clinics of Florida (MMTC) in Gainesville, Ocala, and The Villages. To date, at the 3 locations from which we will recruit, medical marijuana physician services are provided to 4653 adults aged 50 years and older, with 3119 having at least 1 recertification appointment or more. Recertification in the state of Florida occurs every 210 days; therefore, we have an adequate number of potential participants to meet the sample size demands for the MMG. NMG participants will be race-sex–matched adults aged 50 years and older who endorse chronic or severe pain, recruited from the community using flyers and handouts, newspaper advertisements, internet advertisements, social media, in-person lectures and events, and contact by mail, email, and through the infrastructure and support of Oak Hammock at the University of Florida (UF), a residential retirement community.

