After sobriety is ascertained, the task continues with a “warm-up” period using a dual-brake program vehicle (a 2019 Toyota Camry or 2020 Toyota Corolla) in a parking lot. The evaluator will review the general controls for mirrors, seats, and automatic transmission shift. Drivers will perform simple maneuvers and practice perpendicular or angled parking for approximately 3 minutes. The course is designed to progress from simple to moderate and then high-complexity environments. The parking lot or “off-road” area transitions directly into a residential or simple driving environment. To ensure adequate exposure within each level of difficulty, the course is designed to include at least 3 examples of each type of maneuver within each level of difficulty. Multimedia Appendix 1 contains road course documentation and scoring details. The assessments will take place during daylight hours from mid-morning through late afternoon—approximately 9 AM to 4 PM. Assessments will be cancelled if the clinical evaluator deems the conditions unsafe due to inclement weather or unsafe road conditions. The complete course consists of 49 maneuvers through Gainesville, Florida. The driving performance form is designed so a single evaluator can document observed driving errors adequately and remain attentive to the driver and surrounding conditions. The fixed route ensures all participants are given the same maneuvers. The evaluator will check observed errors from a list of behaviors under each maneuver. The SMS is the total number of points accumulated over the set number of maneuvers divided by the total possible number of points (49 maneuvers × 3 = 147 possible points, indicating perfect driving). Participants will be compensated US $50 for this assessment and an additional US $20 as a transportation supplement for expenses such as gas or rideshare fees spent traveling to the Smart House.

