### Study Conditions

#### Exposure: Medical Marijuana Group

Any patient who has been certified for medical marijuana use and has held an active medical marijuana card in the state of Florida for at least 12 months, is aged 50 years or older, endorses chronic or severe pain, and reports using medical marijuana purchased through the state of Florida dispensation system daily or most days of the week for the past year, as documented by purchases over the course of the year in the OMMU database, has an active Florida driver’s license and the visual acuity to perform the task with or without vision corrective apparatus (glasses or contacts). Medical marijuana was legalized in Florida in January 2017. Per Florida state statute 381.986, residents of Florida have access to marijuana for medical use if authorized by a qualified medical marijuana physician. All medical marijuana patients must register with the state for access to medical marijuana, which includes the certification process identifying a qualifying condition, the reason the patient is authorized to use medical marijuana, and tracking all purchases through the OMMU. Qualified medical marijuana patients are allowed to purchase up to 2.5 ounces of smokable flower every 35 days, and limits on the milligrams of all other routes of administration are set by the physician. Patients must be recertified to use medical marijuana every 210 days (7 months). We will track dosage, frequency, type of product used (high vs low cannabidiol/THC), and route of administration. All medical marijuana participants will be recruited from the MMTC, our medical marijuana recruitment partner. Participants will be allowed to complete the drive regardless of a negative or positive urine screen for opioid use. Our current data suggests that approximately 40% of medical marijuana patients will also test positive for opioid use.

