#### No Marijuana Use Group (Past 10 Years)

NMG participants will be race-sex–matched adults aged 50 years and older who endorse chronic or severe pain, recruited from the community using flyers and handouts, newspaper advertisements, internet advertisements, social media, in-person lectures and events, and contact by mail, email, and the infrastructure and support of Oak Hammock at the UF—a residential retirement community. We will also phone individuals enrolled in the UF Clinical and Translational Science Institute’s Integrated Data Repository, a database organizing clinical information across UF Health’s clinical and research programs [42]. Individuals enrolled in UF Health services or taking part in UF research studies can provide consent to be contacted within this system, and data can be queried using National Institutes of Health’s Informatics for Integrating Biology and the Bedside tool, which provides researchers with a HIPAA-compliant and UF Institutional Review Board–approved limited dataset [43]. In querying this dataset for adults aged 55-84 years (adults aged 45-54 years were grouped together and thus excluded from the query) with who endorse chronic or severe nonmalignant pain, the tool reported 7463 potential participants who have consented to be contacted for research participation. Participants will be allowed to complete the drive regardless of a negative or positive urine screen for opioid use. Our current data suggests that approximately 25% of control participants will also test positive for opioid use, with literature estimating of up to 50% of patients with chronic or severe nonmalignant pain using opioids.

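### All drives are scored on one fixed Gainesville route, but the two groups are recruited through different catchments, so route familiarity may confound the group contrast and nothing stated measures or reliably controls it

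*Protocol article*

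**What the plan says.** **Outcome.** Under Open-Road Course Driving Performance Test: "Our standardized road course is a fixed route in Gainesville, Florida, with a gradual progression of driving difficulty". Under Assessment Session 2: "The fixed route ensures all participants are given the same maneuvers".

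**Marijuana group (MMG).** Study Setting and Recruitment: "Participants will be recruited from Medical Marijuana Treatment Clinics of Florida (MMTC) in Gainesville, Ocala, and The Villages". The exposure-group section makes this source exclusive: "All medical marijuana participants will be recruited from the MMTC, our medical marijuana recruitment partner".

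**Control group (NMG).** General channels come first: "recruited from the community using flyers and handouts, newspaper advertisements, internet advertisements, social media, in-person lectures and events", plus mail and email. No place is given for any of these. Two institutional sources are then named. One is "the infrastructure and support of Oak Hammock at the University of Florida (UF), a residential retirement community". The other is the university's data repository: "We will also phone individuals enrolled in the UF Clinical and Translational Science" Institute's repository, of which the article says "Individuals enrolled in UF Health services or taking part in UF research studies can provide consent to be contacted within this system". The repository is the only control source given a size, 7463 contactable people.

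**Comparability.** The Participants section matches on race and sex and balances age to within one year. The Data Analysis Plan compares the groups on potential confounders and keeps as covariates the medical and demographic variables that prove to be significant predictors. The Hypothesis 1a and 1b section starts with an unadjusted two-sample t test and follows it with an ANCOVA adjusting for significant sociodemographic, driving, behavioral and clinical variables. Residence, recruitment site and familiarity with the course area are not named among the matching factors, the first-session measures or the covariates.

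**The concern.** A fixed public route standardizes the task, but it does not make the task equally familiar to everyone, and there is no variation in route over which local knowledge could average out. Several scored items plausibly depend on knowing the roads. Adjustment-to-stimuli errors include wrong lane choice from signage and failure to follow the evaluator's directions. Under Scoring Criteria, having to repeat an instruction lowers a maneuver from 3 to 1. The warm-up takes place in a parking lot and covers the vehicle, not the route.

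If the share of drivers who know the area differs between groups, part of any SMS difference would come from where people live and not from marijuana. Blinding the evaluator does not help, because the score difference would be genuine but have another cause. The results are meant to inform risk screening and guidelines for use, so this alternative explanation matters. The limitations section sets representativeness aside because the aim is an exposure effect. That puts the whole weight on comparability between groups, and catchment is not discussed there.

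**Working it through.** The plan gives no figure on this point. The check therefore compares sections and then illustrates how large the bias could be.

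**Step 1. Catchments side by side**

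| | MMG | NMG |
|---|---|---|
| Source | Clinics only | Advertising and outreach, plus two institutional sources |
| Stated places | Gainesville, Ocala, The Villages | University of Florida links for the two institutional sources; none stated for the rest |
| Split by place | Not given | Not given |

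Two of the three MMG towns are not the test town. Nothing stated brings the controls' locality into line with that.

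**Step 2. Illustrative bias (all inputs assumed)**

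- Bias in SD = (difference between groups in the share unfamiliar with the area) × (effect of unfamiliarity on SMS, in SD).
- Standard error of the standardized difference with 125 per group = √(2/125) = 0.126.
- Rejection probability with no true effect = P(|Z + bias/0.126| > 1.96). The two-sided 5% level is my assumption.

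| Difference in share | Effect (SD) | Bias (SD) | Bias/SE | False-positive rate |
|---|---|---|---|---|
| 10 points | 0.20 | 0.02 | 0.16 | 5.3% |
| 25 points | 0.35 | 0.09 | 0.69 | 10.6% |
| 40 points | 0.30 | 0.12 | 0.95 | 16% |
| 50 points | 0.35 | 0.175 | 1.38 | 28% |
| 60 points | 0.50 | 0.30 | 2.37 | 66% |

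For scale, the difference detectable with 80% power at this size is (1.96 + 0.84) × 0.126 = 0.354 SD. The assumed range therefore runs from negligible to most of the detectable difference. The calculation is symmetric: a bias of either sign inflates false positives equally when there is no true effect, and its sign decides whether a real effect is exaggerated or hidden.

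**Step 3. Would entry by significance catch it?**

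Suppose familiarity were recorded, half of the 250 were unfamiliar, and it were screened alone against SMS. The standard error is 2/√250 = 0.126. The chance of reaching significance is then:

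- effect 0.20 SD: ratio 1.58, about 35%
- effect 0.35 SD: ratio 2.77, about 79%
- effect 0.50 SD: ratio 3.95, about 98%

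A large effect would nearly always enter the model. A small or moderate one could be dropped and still bias the contrast. If familiarity is not recorded, it cannot enter at all.

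**The case against.** The strongest reply is that this is only a possibility.

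- **Residence.** No section gives residence by group. Clinic town is not home town, some MMG participants will be from Gainesville, and most control channels have no stated location and could reach Ocala and The Villages. The repository's catchment is not stated either. This stands. A reader might infer that familiarity *is* confounded with marijuana use, but the documents support only that it may be.
- **Direction.** A reader might infer that the bias favors finding harm from marijuana. The documents do not show this. The scored errors also include incomplete stops, speeding and omitted mirror or intersection checks, which familiar drivers might commit more often from habit, and the evaluator gives directions during the drive. This stands.
- **Size.** It is tempting to express the bias as a share of the planned effect f=0.20 (d=0.40). The Sample Size section ties that value to the aim 2 subgroups. For the MMG-NMG contrast it anticipates a medium effect based on r=0.459, so the comparison would not be valid.
- **Existing handling.** The plan does compare groups on potential confounders, admits driving variables as a class, reports results with and without adjustment, and collects contact information from which locality might be recovered. This helps in part. Step 3 shows the limit of selection by significance, and an address does not say how often someone drives the course area.
- **Condensation.** The article may leave the intake questionnaire and covariate list to fuller documents, so silence is weak evidence that familiarity goes unrecorded. But recruitment and matching are set out here, and a later analysis plan cannot adjust for something that was not collected.

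**Conclusion.** The point holds as a possible confounder that the stated design neither prevents nor names for measurement. It rests on four stated facts: one fixed route, an exclusive three-town source for the exposed group, university-linked institutional sources for controls, and comparability limited to race, sex, age and covariates chosen by significance. It also rests on a plausible but undocumented link between some scored items and local knowledge. Size and direction cannot be determined from the documents. On assumed inputs, the bias runs from 0.02 to 0.30 SD and the false-positive rate from about 5% to 66%. That range shows that the problem could be trivial or serious; it is not an estimate. The reason to act is that measuring familiarity is cheap and 250 − 30 = 220 participants were still to be enrolled at the time of writing.

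**What to change.** 1. At the first assessment session, record home ZIP code and how often the participant drives in the course area.
2. Specify in advance that this familiarity variable enters the primary ANCOVA regardless of its significance.
3. In Study Setting and Recruitment and in the control-group section, state that the control advertising already planned will be directed to Gainesville, Ocala and The Villages, so that locality is roughly balanced with the MMG.
4. Add a sensitivity analysis of the MMG-NMG contrast restricted to Gainesville-area participants. It will have less power and should be read for consistency of the estimate.
5. For the 30 already enrolled, recover locality from contact information where possible and ask the driving-frequency question retrospectively.

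The cost is two intake questions, one model degree of freedom and possibly slower control recruitment. The course and its scoring do not change. If familiarity proves balanced or unrelated to SMS, the report can say so with data.

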#### Lane Maintenance Errors

These refer to the lateral positioning of the vehicle during driving maneuvers such as turns, straight driving, lane changes, and while stopped, reflecting the ability to maintain steering control.

#### Speed Regulation Errors

These reflect the ability to follow and maintain speed limits and adequately control acceleration and braking features of the vehicle; examples include not coming to a complete stop at a stop sign, traveling too slowly or too fast, inadequate merging speed, and abrupt or inappropriate braking or acceleration.

#### Adjustment-to-Stimuli Errors

These capture the ability to adjust appropriately to changing road sign information, other vehicle movements, and pedestrian movements, and to recognize potential hazards; examples include not adjusting speed for posted limits, not following proper directions given by the evaluator, choosing an improper lane from posted signage, and improper responses to traffic, pedestrian, or cyclist movement.

#### Yielding Errors

These refer to the ability to recognize common rules of road safety and to give the right-of-way when appropriate; these are assessed at 4-way or 2-way stop intersections when other vehicles are present, during right turns on red, and during merges.

#### Signaling Errors

These reflect the proper use of turn signals; examples include leaving the turn signal on, not using the turn signal when turning, using the turn signal inappropriately (eg, using the wrong signal for a given turn), or signaling for too short a duration before a maneuver.

#### Vehicle Positioning Errors

These refer to the anterior-posterior position in relation to other vehicles, objects, and pavement markings; they capture following distance during forward movement and vehicle spacing during lane changes and merges. Examples include traveling too closely or tailgating, having an inadequate space cushion during a merge or lane change, and stopping across a crosswalk or too far back from either pavement markings or other vehicles.

#### Visual Scanning Errors

These refer to demonstration of visual scanning of the driving environment; examples include not checking blind spots or mirrors during turns and lane changes and not looking left or right before proceeding through an intersection.

#### Gap Acceptance Errors

These refer to choosing an appropriately safe time and spacing distance to cross in front of oncoming traffic in the context of an unprotected left turn; these are based on evaluator judgment given the speed of oncoming traffic and the number of lanes to be crossed.

#### Scoring Criteria

Scoring in this study is based on assessing driving errors to discern how participants perform on the road and to identify driving performance deficits. The 8 driving errors are being measured on a scale from 0 (physical intervention indicating very poor driving performance) to 3 (no driving errors indicating good driving performance). For each maneuver, a maximum score of 3 is given if no errors are committed. Specifically, the scoring is as follows: 3 indicates no errors, 2 indicates any error in any driving behavior for the given maneuver, 1 indicates that the evaluator must use verbal cues or repeat instructions (not hearing-related) to modify or change driving behavior, and 0 indicates that physical intervention (such as grabbing the steering wheel or using the auxiliary brake) is required. At the end of the driving course, the sum of the points attained is computed as the sum of maneuvers score (SMS), ranging from 0 to 147, with 147 indicating a perfect driving score (zero errors) [34,35], which provides detailed information to identify deficits in the participants’ driving performance.

### Study Setting and Recruitment

Participants will be recruited from Medical Marijuana Treatment Clinics of Florida (MMTC) in Gainesville, Ocala, and The Villages. To date, at the 3 locations from which we will recruit, medical marijuana physician services are provided to 4653 adults aged 50 years and older, with 3119 having at least 1 recertification appointment or more. Recertification in the state of Florida occurs every 210 days; therefore, we have an adequate number of potential participants to meet the sample size demands for the MMG. NMG participants will be race-sex–matched adults aged 50 years and older who endorse chronic or severe pain, recruited from the community using flyers and handouts, newspaper advertisements, internet advertisements, social media, in-person lectures and events, and contact by mail, email, and through the infrastructure and support of Oak Hammock at the University of Florida (UF), a residential retirement community.

### Retention

First, we will develop a strong collaborative relationship between participants and members of the research team. Second, participants welcome participation when they know that they are contributing and that their efforts have the potential to improve other people’s experiences. Therefore, we will send information on pain management, other related resources, and local events that highlight the benefits of research. Finally, to enhance retention for this proposal, we will obtain additional contact information, communication preferences, and use dedicated research staff time for connecting, tracking, and follow-up.

### Sample Size and Power

Power estimates for this study are based on the number needed for the subanalysis to ensure we have sufficient power to answer aim 2. Using G*Power for the *F* test, we calculated the sample size for a small effect size (*f*=0.20) based on the expectation of a smaller effect size for subgroup analyses than for the main analyses [36]. Therefore, with an α of 0.5 and power set at 80%, a total sample size of 198 is needed to detect a small effect between subgroups of medical marijuana only, medical marijuana and prescription opioids, prescription opioids only, and no use at all. However, to ensure we have the full sample needed, we are planning for a potential early termination rate (eg, drive not completed due to intoxication or other reasons) of 5%, which indicates we need a sample size of 250—as 198 + 10 (5%) = 250 (125 per group). We anticipate a medium effect size for aim 1 based on the first ROAD ACE (Reactions of Older Adults Driving After Cannabis Exposure) project (1R21DA048067) that examined driving errors and medical marijuana 7-day pattern of use in a driving simulator. We found a Pearson *r*=0.459, which is equal to a medium effect size (see preliminary data above). Therefore, we will have sufficient power to test the effects in aims 1 and 2.

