#### Hypothesis 2b

Then we will check the combined effect of medical marijuana and prescription opioid on driving performance (SMS) using ANCOVA. The best fitted model we find in aim 1 will be performed in the subgroup of medical marijuana users and non–marijuana users, respectively. Thus, we will have a clear picture of the driving performance in the 4 groups: medical marijuana and prescription opioid, medical marijuana without prescription opioid, prescription opioid without medical marijuana, and no medical marijuana no prescription opioid. Thus, the combined effect can be determined.

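### The 80% power stated for aim 2 fits one whole-sample contrast, but hypothesis 2b is analysed within marijuana groups of 125, where power is about 58% and 48% if f=0.20 means d=0.40 in each

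*Protocol article*

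**What the plan says.** The Sample Size and Power section says the study is sized for the aim 2 subanalysis. The calculation is described as "Using G*Power for the *F* test", with f=0.20 and "with an α of 0.5 and power set at 80"%. The result is that "a total sample size of 198 is needed to detect a small effect between subgroups of medical marijuana only, medical marijuana and prescription opioids", followed by the opioid-only and no-use subgroups. The planned total is 250, or 125 per marijuana group, and the section ends by claiming sufficient power for both aims.

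The Hypothesis 2b section describes the analysis: "The best fitted model we find in aim 1 will be performed in the subgroup of medical marijuana users and non–marijuana users, respectively". From these fits the protocol expects a picture of the four marijuana-by-opioid groups, and hence the combined effect.

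Opioid use is observed, not assigned. The Study Conditions sections expect that "approximately 40% of medical marijuana patients will also test positive for opioid use" and that "approximately 25% of control participants will also test positive for opioid use". For the controls they also mention a literature figure of up to 50%.

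**The concern.** The test behind 198 and the analysis planned for 2b are different. A whole-sample calculation uses everyone in one contrast. The 2b fits use at most 125 people each, split unequally by opioid status, and the power section uses neither the halved sample nor the opioid rates.

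Aim 2 is the stated reason for the sample size. If each 2b comparison has roughly even odds of missing an effect of the planned size, a non-significant opioid effect in one group may be read as no effect there. Significance in one group but not the other may be read as a combined effect. Neither inference would be sound, and the article's Conclusions say these data will inform risk screening protocols and intervention targets.

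**Working it through.** **Inputs from the protocol article.** f=0.20, 80% power, N=198, planned total 250 (125 per group), 5% early termination; opioid shares 40% (medical marijuana group, MMG) and 25% (no marijuana group, NMG), with 50% as the upper literature figure.

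**Assumptions.** Two-sided alpha 0.05: the article prints 0.5, but a single-df test at 0.5 would need only N=54. The within-group effect is d=2f=0.40, the conversion for two equal groups. Power is unadjusted unless stated.

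**1. Reproducing 198.** Noncentral F with noncentrality f²N = 0.04 × 198 = 7.92.
- 1 numerator df: power 79.97% (exact N is 199; the normal approximation gives 198).
- 2 df: N=244 needed.
- 3 df (four-group omnibus): N=277 needed; power 64% at 198 and 75% at 250.

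At alpha 0.05, 198 therefore corresponds to one 1-df contrast on the whole sample.

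**2. Expected cells.** MMG: 0.40 × 125 = 50, leaving 75. NMG: 0.25 × 125 ≈ 31, leaving 94.

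**3. Power within each group.** Noncentral t, δ = d / √(1/n₁ + 1/n₂), d=0.40.

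| Comparison | Cells | δ | Power |
|---|---|---|---|
| MMG | 50 vs 75 | 0.40/0.1826 = 2.19 | 58.5% |
| NMG | 31 vs 94 | 0.40/0.2071 = 1.93 | 48.3% |
| MMG after 5% loss | 48 vs 71 | 2.14 | 56.5% |
| NMG after 5% loss | 30 vs 89 | 1.89 | 46.8% |
| NMG at 50% opioid use | 62 vs 63 | 2.24 | 60.2% |
| Pooled, hypothesis 2a | 81 vs 169 | 2.96 | 83.9% |
| Pooled after 5% loss | 78 vs 160 | 2.90 | 82% |

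Minimum detectable d at 80% power is 0.516 (MMG) and 0.585 (NMG); rounded up, 0.52 and 0.59.

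**4. Covariates.** If they explain an assumed 20% of outcome variance, d becomes 0.40/√0.80 = 0.447 and power is 68% and 57%. Reaching 80% would need about 40% (MMG) or 53% (NMG) of variance explained. The article gives no such figure.

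**5. Other patterns with four-group f=0.20.** f² is the weighted variance of the cell means, in SD units, with the cells above.
- Deficit only in the marijuana-plus-opioid cell (50/250 = 0.2): f² = 0.2 × 0.8 × d² = 0.04, so d=0.50 and MMG power is about 78%.
- Equal additive effects e of marijuana and opioids (cell means 2e, e, e, 0): f² = (1.224 − 0.824²)e² = 0.545e² = 0.04, so e=0.27 and power is about 31% (MMG) and 25% (NMG).

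**6. The combined-effect contrast.** For the difference between the two opioid effects, SE = √(1/50 + 1/75 + 1/31 + 1/94) = 0.276 SD. A difference of 0.40 SD gives δ = 1.45 and power of about 30%. The difference detectable with 80% power is about 0.78 SD.

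**7. Discordant results.** If the opioid effect were 0.40 SD in both groups, both tests would be significant with probability 0.585 × 0.483 = 0.28. Exactly one would be significant with probability 0.585 × 0.517 + 0.415 × 0.483 = 0.50.

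**The case against.** The strongest reply is that the protocol never states an opioid effect of d=0.40 within each marijuana group. Its f=0.20 refers to four subgroups, and step 5 shows that this f is compatible with quite different within-group effects. This stands: 58% and 48% describe one scenario and should not be presented as the power of 2b.

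Second, the Hypothesis 2b section opens by announcing an ANCOVA of the combined effect and closes with the same four groups as the power section. It does not say that a p-value within each group decides the hypothesis, nor explicitly that an opioid term joins the aim 1 model. The numerator degrees of freedom are unstated, and this is a condensed article. A reader might infer that the plan excludes any joint four-group test; the text does not go that far. Such a test would not rescue the claim, however: at 3 df it has 75% power at 250.

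Third, the planned ANCOVA adjusts for covariates, which should raise power. That is correct, but the gain required is large and the article assumes none.

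Fourth, a single interaction contrast sized at f=0.20 could be what was intended. In balanced cells that is a difference of 0.80 SD between the opioid effects. It has about 82% power at 250 with the expected cells, but it is again a whole-sample 1-df contrast and not the separate fits described.

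**Conclusion.** The point holds for hypothesis 2b. The stated 80% is supported only if aim 2 is a single 1-df contrast on the whole sample. With the protocol's own opioid rates and d=0.40 assumed in each group, unadjusted power is about 58% in MMG and 48% in NMG. The range across four-group patterns is about 31% to 78% in MMG.

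A reader might go further and infer that aim 2 as a whole is underpowered or that 250 is too few. The documents do not support that: the pooled opioid comparison of hypothesis 2a keeps about 84% (82% after 5% loss) at d=0.40. What fails is the claim of sufficient power for 2b, and the idea that separate fits can by themselves settle the combined effect. The result rests on alpha 0.05, the stated opioid rates and the assumed d.

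**What to change.** **Sample Size and Power.** Stop claiming about 80% power for 2b. For the pooled 2a comparison, state about 84% at d=0.40 (81 vs 169), or 82% after 5% loss. For 2b, give the minimum detectable d at 80% power at the expected cells, about 0.52 (MMG) and 0.59 (NMG). Any power quoted at d=0.40 should be labelled as an assumption and shown with a range.

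**Hypothesis 2b.** Judge the combined effect by the marijuana-by-opioid contrast in one model of all 250 participants, with its 95% confidence interval. State that power is about 30% for a difference in opioid effects of 0.40 SD and that the detectable difference is about 0.78 SD. Report the opioid effect within each marijuana group as an estimate with a 95% confidence interval. Say that significance in one group but not the other, or non-significance, is not evidence about the combined effect.

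**Cost.** Text changes in two sections and one additional model term. No extra participants or data are needed. The stated power for 2b becomes less favourable.

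### The sample size of 198 does not follow from the stated four-subgroup F test, which has about 73–75% power, not 80%, at the planned enrolment

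*Protocol article*

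**What the plan says.** The section Sample Size and Power bases the whole study on aim 2. It describes a G*Power F test for a "small effect size (*f*=0.20"), "with an α of 0.5 and power set at 80"%, and concludes that "a total sample size of 198 is needed to detect a small effect between subgroups of medical marijuana only" and the others it lists. The full list is four: "subgroups of medical marijuana only, medical marijuana and prescription opioids, prescription opioids only, and no use at all". It gives neither the numerator degrees of freedom nor a specific contrast.

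The section then allows 5% for early termination, adds 10 to 198, reports the result as 250 (125 per group), and ends: "Therefore, we will have sufficient power to test the effects in aims 1 and 2".

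Elsewhere the article gives the expected opioid shares: "approximately 40% of medical marijuana patients will also test positive for opioid use" (Exposure: Medical Marijuana Group) and "approximately 25% of control participants will also test positive for opioid use" (No Marijuana Use Group). Hypothesis 2a is a two-sample t test of opioid users against non-users, ignoring marijuana status. Hypothesis 2b fits the aim 1 ANCOVA model separately in marijuana users and non-users to describe the four groups.

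**The concern.** An F test across four groups has 3 numerator df, and at a given f it needs clearly more participants than a 1-df test. The figure 198 looks too small for four groups at the usual alpha of 0.05 and far too large at the printed 0.5.

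This is the only sample-size calculation in the article, and the closing statement of sufficient power for both aims depends on it. If the four-subgroup comparison came out null, a reader would take it as having had 80% power when it had less. The step from 198 to 250 does not settle the matter, because the sum printed for it is wrong.

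**Working it through.** **Inputs from the article.** f = 0.20, power 80%, alpha printed as 0.5, four subgroups, N = 198, enrolment 250, early termination 5%, opioid shares 40% and 25%.

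**Method.** Noncentral F with noncentrality λ = N·f², df2 = N − number of groups, and power = P(F′(df1, df2, λ) > critical value). This is the usual fixed-effects ANOVA calculation.

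**1. Can 198 be reproduced?** N required at f = 0.20 and 80% power:

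| Groups | df1 | alpha | N required | Matches 198? |
|---|---|---|---|---|
| 4 | 3 | 0.5 (as printed) | 76 | no |
| 4 | 3 | 0.05 | 277 (280 with equal cells) | no |
| 2 | 1 | 0.05 | 199 | yes, within rounding |
| 4 | 1 | 0.05 | 199 | yes, within rounding |
| 3 or 4 | 2 | 0.10 | 196 (198 with three equal groups) | yes, but nothing in the text suggests it |

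The 1-df match is close. Power at 198 is 0.7997. The normal approximation with d = 2f = 0.40 gives 2 × (1.960 + 0.842)² / 0.40² = 98.1, hence 99 per group and 2 × 99 = 198.

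**2. Power of the four-subgroup test (df1 = 3, alpha 0.05, f = 0.20).**
- N = 198: λ = 198 × 0.04 = 7.92, power 63.9%.
- N = 208 (the correct sum of 198 + 10): λ = 8.32, power 66.4%.
- N = 237 (250 × 0.95 = 237.5, rounded down): λ = 9.48, power 72.8%.
- N = 250: λ = 10.0, power 75.4%.

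The smallest f detectable with 80% power is 0.216 at 237 and 0.210 at 250.

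**3. Effect of the printed alpha.** With alpha 0.5, four groups and N = 198, power is 96%. The misprint makes the test easier to pass and cannot explain a shortfall.

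**4. Hypothesis 2a (1 df).** Assume d = 0.40, my reading of f = 0.20 for two groups. The opioid share overall is (40% + 25%) / 2 = 32.5%.
- N = 237: 77 against 160, noncentrality 0.40 / √(1/77 + 1/160) = 2.88, power 82%.
- N = 250: 81 against 169, noncentrality 2.96, power 84%.

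**5. If a 1-df marijuana-by-opioid interaction was meant.** In a balanced 2×2, f = 0.20 for the interaction is a difference-in-differences of 4 × 0.20 = 0.80 SD. With 237 evaluable and the stated opioid shares, the cells are about 47.4, 71.1, 29.6 and 88.9. The standard error is √(1/47.4 + 1/71.1 + 1/29.6 + 1/88.9) = 0.283 SD. The detectable difference at 80% power is (1.97 + 0.84) × 0.283 ≈ 0.80 SD.

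**The case against.** The strongest reply is that the gap at the size actually planned is small and may close. The study enrols 250, not 198, and the detectable f there is 0.21 to 0.216 against a planned 0.20. The Data Analysis Plan uses ANCOVA partly to gain power. If f = 0.20 is on the unadjusted scale, covariates explaining about 15% of the variance bring power at 237 to 80% (λ = 237 × 0.04 / 0.85 = 11.15), and about 10% do so at 250 (λ = 250 × 0.04 / 0.90 = 11.11). This stands as a possibility. The article does not say which scale f is on or how much variance it expects covariates to explain, so it cannot support the stated 80%.

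Four stronger readings are tempting, and the document does not support them:
- A reader might infer that the alpha of 0.5 causes the low power. It would raise power.
- A reader might infer that aim 2 as a whole is underpowered. Hypothesis 2a is part of aim 2 and reaches 80% at the planned size under the assumptions in step 4.
- A reader might infer that 198 came from a two-group calculation. A 1-df contrast within four groups gives the same number, and the article does not state the df.
- A reader might infer that equal cells were assumed or an interaction test planned. The article states neither; hypothesis 2b describes separate fits in users and non-users.

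**Conclusion.** The point holds for the four-subgroup comparison. The stated inputs do not yield 198, which fits a 1-df test at alpha 0.05. The comparison as described has 64% power at 198 and 73–75% at the planned enrolment, a shortfall of 5 to 7 points before any covariate gain. This rests on reading the comparison of four subgroups as an omnibus 3-df F test at alpha 0.05.

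The printed alpha is a separate error, most likely a misprint for 0.05, since 198 fits 0.05 with 1 df. The closing statement of sufficient power is too broad for aim 2, though it is tenable for hypothesis 2a if f = 0.20 means d = 0.4 and the opioid shares are as stated. The interaction figure applies only if the authors intended that contrast. At about 0.80 SD, it could not be called a small effect.

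**What to change.** Rewrite the Sample Size and Power paragraph, with no added enrolment:

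1. Correct alpha to 0.05.
2. State the numerator df and the contrast that 198 powers.
3. Restate power for the four-subgroup comparison at the planned 250: 73–75% at f = 0.20, with a detectable f of 0.21 to 0.216. If a covariate gain is claimed, state the variance assumed to be explained.
4. Limit the sufficiency claim for aim 2 to the tests that reach 80%, such as hypothesis 2a, and give the assumptions.
5. Correct the sum: 198 + 10 is 208. Give the actual reason for 250.
6. If a 1-df marijuana-by-opioid interaction is intended, say so, report the detectable difference-in-differences (about 0.80 SD at 237 with the 40% and 25% opioid shares), and drop the description of it as small.

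The cost is one reworded paragraph and a less favourable power statement for the four-subgroup comparison. No test, endpoint or enrolment target changes.
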